### Participants and eligibility requirements

Participants recruited for this study will be female patients with breast cancer or gynecological cancer who will undergo a standard of care chemotherapy treatment as directed by their oncologist. Participants are all women who are undergoing adjuvant therapy, meaning that gynecological and breast cancer patients are not presenting clinical evidence of disease (non-metastatic) therefore can be considered from the same population for modeling purposes. Additionally, treatment regimens for these patient populations are similar based on NCCN guidelines which warrants modeling them together. Participants who are cleared by their oncologist to participate will be recruited through informative pamphlets and by oncology nurses trained in research and human subjects protection in Prisma Health System’s Cancer Institute at Greenville Memorial Hospital, as well as Prisma Health affiliated oncologists’ offices. Participants will be informed of the study’s purpose, availability, timeline, and potentially associated minimal risks. Study staff will then obtain written informed consent from participants who agree to participate and before any data collection. Patient inclusion and exclusion criteria are listed in Table 1.

**Table 1 pone.0315351.t001:** Inclusion and exclusion criteria.

Inclusion Criteria
Female patients diagnosed with breast cancer or gynecological cancer without distant metastasis
Age > 20 years old
Able to perform exercise on a stationary cycle ergometer at moderate intensities for a maximum of 15 minutes
Hemoglobin (Hb) values > 10 g/dl at baseline
Alanine aminotransferase (ALT) and Aspartate transferase (AST) values less than 2.5X the upper limit of normal by institutional standards
Godin-Shephard Leisure Time Physical Activity Questionnaire (GLTEQ) score of 14 or higher
Exclusion Criteria
Metastatic breast or gynecological cancer
Clinically advanced cardiovascular disease or pulmonary disease or disease requiring continuous oxygen supplementation
Greater than 2 centimeters of subcutaneous adipose tissue on the anterior thigh
Inability to walk or stand, movement disorders, spinal cord injuries
Autoimmune disorders
Pregnant or breastfeeding
Mini-Mental State Examination (MMSE) score < 24
History of chemotherapy within 5 years prior to beginning participation

### Observational protocol for first and subsequent visits

Before starting chemotherapy, patients will undergo baseline testing that includes a lactate threshold test and an ON-OFF kinetics exercise test. The lactate threshold test will determine the power output (110% power at lactate threshold, P_LT+_) to be used for the follow-up baseline on-off kinetics test (ON-OFF). The ON-OFF kinetics test will take place at least 24 hours after the lactate threshold test and consist of 3 cycles of 2 minutes at P_LT+_ and 2 minutes of complete rest. Whole body O_2_ uptake and CO_2_ production will be captured via a metabolic cart during each test. Testing will take no more than 60 minutes per session, with a maximum study total of 300 minutes (about 5 hours) of participation per patient. Patients will be requested to avoid exercise and use of certain substances (tobacco, alcohol, caffeine, and contraindicated medications) 24 hours before testing. If laboratory baseline evaluation cannot be completed prior to the participant’s treatment initiation, treatment will not be delayed, and patients will be waived from the study.

The independent variables in this study are drug regimen and number of chemotherapy treatments. The dependent variables in this study will be the changes in O_2_Hb, HHb, and TSI of the vastus lateralis, indicative of mitochondrial oxidative capacity after a bout of cycling. The specific variables measured will be the average recovery kinetics time constant, τ, and TSI. Indirect calorimetry (O2 uptake, CO2 production) also will be captured at rest and during the ON/OFF kinetics as control variable comparisons for whole-body O2 uptake and utilization.

#### Instruments and equipment.

The following devices will be utilized throughout the study: NIRS PortaMon by Artinis (Einsteinweg, Netherlands), Lode Corival (Groningen, Netherlands) stationary bike ergometer, Parvo Medics TrueOne 2400 (Salt Lake City, Utah) metabolic cart, Polar FT7 heart rate (HR) monitor (Kempele, Finland), Lactate Plus analyzer (Edina, Minnesota) and Sonosite Titan Portable Ultrasound System (Bloomfield, Connecticut) for adipose tissue thickness measurement.

#### Fatigue and quality of life surveys.

We will administer the Mini-Mental State Exam (MMSE) [43–45], Brief Fatigue Inventory (BFI) [46], Physical Activity Intake [47,48], PROMIS Global Health [49,50], and GLTPAQ surveys [51] prior to participant engagement in cycling exercises at the beginning of the first visit. We will administer BFI, PROMIS Global Health, and Physical Activity follow-up surveys at the beginning of each individual study session to assess any changes in cancer related fatigue associated with chemotherapy treatment that may develop throughout the study period.

#### Visit #1: Lactate threshold test to tetermine power output, NIRS orientation.

Participants will be asked to wear comfortable exercise clothes with shorts or equivalent so that the NIRS device can be placed directly on the skin. Participants will enter the performance lab and sit at rest in a chair. The NIRS device will be secured to the participant’s leg at a standardized measurement of ⅔ distance along a line from the anterior superior iliac spine to the lateral border of the patella [52]. This distance will be measured and marked medially and laterally on the patient’s leg at a place that will not disrupt signal transmission. At this marked location, an ultrasound probe will be used to measure the subcutaneous adipose tissue thickness (ATT) between the epidermal layer and the muscular layer. If the ATT meets the inclusion/exclusion criteria, the NIRS device will be placed on the vastus lateralis. The ultrasound ATT measurement will be recorded. The NIRS device will be secured to the participant’s leg via double-sided non-latex adhesive tape applied between the device and the leg and lightly secured in position to the skin via non-latex tape. Pictures of the anatomical location of NIRS device placement with a reference tape measure will be taken to standardize placement at every visit.

The patient will then complete the following questionnaires: contact information form, GLTPAQ, MMSE, BFI, PROMIS, and Physical Activity Form. After the completion of the questionnaires, study staff will review the GLTPAQ and Physical Activity form. Study staff will determine the initial power wattage for the test based on the answers to these surveys.

Sitting with both feet on the floor and legs uncrossed, manual blood pressure will be obtained two separate times, five minutes apart after 10 minutes of seated rest. Blood pressure measurements with an average of <140/ < 90 is to be considered safe to continue with testing [20]. After the blood pressure measurement is obtained, the patient will have their temperature measured one time and their height and weight measured two times without shoes. The HR monitor will be fitted on the patient to continuously monitor HR throughout exercise. The rate of perceived exertion (RPE) scale will be explained to the patient. The patient will mount the stationary bike and study staff will help adjust the seat, handlebars, and pedals to the comfort of the patient. Study staff will then place a fitted silicone one-way rebreathing mask on the patient to measure their metabolic data using indirect calorimetry via the metabolic cart that captures expired gasses (O_2_ and CO_2_). Capillary blood lactate levels will be obtained by finger stick for the lactate analyzer.

Participants will sit on the stationary bike for two minutes to capture expired gases and blood lactate levels at rest. At the end of rest, the patient will begin pedaling at a self-selected steady cadence between 60 and 100 RPMs at the initial power wattage determined by study staff. The patient will pedal at this cadence for the remainder of the test. Every three minutes, the power output will increase by 15 Watts. With thirty seconds remaining in each stage, blood lactate levels will be measured in duplicate and study staff will prompt the participant to quantify their effort using the RPE scale. When the duplicate blood lactate measurements exceed 4.0 mmol/L, the participant will complete the current stage and end the test.

After completion of the test, study staff will calculate the power output that is equivalent to 1.1x the wattage at which patients’ lactate exceeded 4.0 mmol/L (P_LT+_). This power output will be used as the exercise intensity for subsequent on-off kinetics testing.

#### Visit #2 + : On-off kinetics testing.

Using the reference photo taken at the first visit, mark the NIRS device location and use the ultrasound to measure and record ATT. If the ATT measurement matches the ATT from the first visit, secure the NIRS device with tape as previously described. The participant will fill out the BFI, PROMIS Global Health, and Physical Activity Follow Up forms and update contact information if needed.

The participants will sit on the bike for a two-minute rest. Participants will begin pedaling for a warmup at 0 Watts for 2 minutes at a self-selected steady cadence of 60–100 RPM. After the 2-minute warm up, the power output will increase to P_LT+_. Participants will cycle at the same self-selected cadence for 2 minutes (“on-kinetics’‘). Thirty seconds before the end of the on-kinetics stage, participants will be asked their RPE. At the end of the 2-minute on-kinetics period, participants will stop pedaling and study staff will remove their non-measured leg from the pedal to rest on a box in a relaxed, extended position to aid in total relaxation and remove any additional movement of the measured leg. During the rest period, participants will remain in recovery sitting on the bike for 2 minutes (“off-kinetics’‘ stage). Participants subsequently will start pedaling at their self-selected cadence for their next 2 minute “on-kinetics” stage, followed by another 2-min “off-kinetics’‘ period. This cycle of exercise followed by rest, referred to as on-off kinetics, will repeat for a total maximum of 3 times, or unless the patient requests to stop.

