## Introduction

In the United States, more than 3.8 million women are currently receiving chemotherapy treatment, or have completed treatment, for breast or gynecological cancer [1]. Fortunately, over the past 25 years, the ability to detect and treat cancer has allowed breast cancer 5-year survivor rates to increase to 85 [1], ovarian cancer 5-year survivor rates to increase to 49% [2], and uterine cancer 5-year survivor rates to increase to 81% [3]. Unfortunately, while chemotherapy has improved survival rates amongst patients with breast and gynecological cancer, side effects include unfavorable body composition changes [4], increases in fatigue [5], reductions in physical functioning [6], and decreased quality of life (QOL) [7]. Many of these symptoms may be due to post-chemotherapy cachexia [8–10]. According to the National Cancer Institute, cachexia is estimated to occur in up to 80% of people with advanced cancer [8,11] and involves reduced size and content of mitochondria [12,13] and subsequent deterioration of mitochondrial function and its oxidative capacity associated with reduced energy production for physical functioning [9,10,14]. Cachexia has negative implications for patients with breast and gynecologic cancer; therefore, the increase in survivorship has been an increase in focus on understanding mitochondrial dysfunction, with the aim to understand how to improve quality of life for [10].

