### Outcome measures

#### Collection of biometrics at each visit.

Study staff will measure O2Hb, HHb, and TSI, via the NIRS PortaMon device during the on-off kinetics protocol. We also will measure ventilatory whole-body components including O_2_ and CO_2_ via the Parvomedics metabolic cart. Participants’ perceived exertion to the exercise will be measured via RPE during every exercise stage.

NIRS data will be collected using Artinis Medical System’s Oxysoft software at a frequency of 10hz. A differential pathlength factor (DPF) value of 4 will be selected, as recommended by Artinis (Einsteinweg, Netherlands). The PortaMon will be placed on the vastus lateralis of participants for a period of at least 10 minutes prior to beginning exercise in accordance with the recommendation of Cortese L, et al. to allow calibration of the PortaMon [53].

Throughout data collection, researchers will closely observe for excess movement from participants that may affect the data collection. These sections will be removed from analysis. After data collection, a moving average with a filter width of 1.5 seconds will be applied to smooth leg movement artifacts that occurred during cycling. Data cleaning and analysis will be conducted using R (R Core Team, 2020] and RStudio (Rstudio Team, 2020].

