A few limitations are to be considered regarding the validity of the PortaMon by Artinis Medical Systems. First, the device is designed to accurately penetrate 20 mm of depth through adipose tissue and into the muscle belly. If the subcutaneous adipose tissue thickness is greater than 20 mm, the infrared signal from the device will not penetrate the skeletal muscle body and be unable to obtain accurate measurements. Our protocol minimizes this concern by excluding participants who have greater than 20 mm adipose tissue subcutaneous to the vastus lateralis, and by standardizing device placement on the leg from test to test to increase reliability and validity of repeated measures measurements. Ambient light can interfere with the signal quality, however Oxysoft provides real-time data acquisition (DAQ) measurements. Using the manufacturer’s recommendation, channels with DAQ higher than 97% will be removed from analysis.

Results from this pilot study will provide information on the feasibility of capturing on/off kinetics mitochondrial function data longitudinally using NIRS in patients newly diagnosed with breast or gynecological cancer, provide preliminary data for future extramural funding, and inform the scientific community of results through dissemination via conference presentations and peer-reviewed journal publications.

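### After the eligibility check, fat thickness under the sensor is used only as an undefined match to visit 1 and enters neither stated model, which leaves ΔO2Hb and ΔHHb open to an optical artefact

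*Protocol article*

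**What the plan says.** At visit 1 ATT is measured by ultrasound at the sensor site and serves as an eligibility check: "If the ATT meets the inclusion/exclusion criteria, the NIRS device will be placed on the vastus lateralis". The value is kept: "The ultrasound ATT measurement will be recorded". Table 1 lists as an exclusion: "Greater than 2 centimeters of subcutaneous adipose tissue on the anterior thigh". A thickness of exactly 20 mm is therefore eligible.

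At each later visit, under the heading for on-off kinetics testing, staff find the site from the reference photo and "use the ultrasound to measure and record ATT". The next instruction is: "If the ATT measurement matches the ATT from the first visit, secure the NIRS device with tape as previously described". The section gives no tolerance and no action for a mismatch.

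The statistical section states two analyses. Aim 1 is a mixed model of τ and the Δ values on the number of chemotherapy treatments, with a random intercept for patients. Aim 2 is a set of ANOVAs between regimens at each cycle. Neither includes ATT. Under collection of biometrics a single pathlength factor is named, "A differential pathlength factor (DPF) value of 4 will be selected", with no correction for fat thickness.

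The Discussion says that "the device is designed to accurately penetrate 20 mm of depth through adipose tissue and into the muscle belly". It regards the exclusion limit and standardized placement as keeping this concern small. The Introduction says of chemotherapy that "side effects include unfavorable body composition changes".

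**The concern.** The quantity that governs how much muscle the sensor sees is recorded at every visit, yet the plan gives it no role in the analysis. The one role it has at follow-up is undefined and causes trouble on each reading.

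- **Literal reading.** If ATT has truly changed, the condition for securing the sensor is not met and the visit yields no NIRS data. A participant needs at least three on-off visits to enter the final analysis, and the target of 30 counts only those who have completed the study. Lost visits could then remove patients selectively, namely those whose body composition changes.
- **Loose reading.** The sensor goes on despite a change, and the change in fat enters the Δ outcomes unadjusted.
- **Moving the probe until ATT matches.** If fat has truly changed, a match is found only at a different site, which conflicts with placement standardized by photograph.

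At stake is the reading of ΔO2Hb and ΔHHb. A drift over cycles, or a difference between regimens, could reflect fat thickness and be reported as a change in mitochondrial capacity.

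**Working it through.** **Inputs from the protocol.** Total sensing depth is 20 mm, fat plus muscle (Discussion). The eligibility limit is ATT up to and including 20 mm (Table 1). The two models are as stated in the statistical section. The sample size of 30 at power 0.8 concerns τ and is not disputed here. It cannot be reproduced, because the slope, its SD, the number of cycles and alpha are not printed.

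**Step 1: sampled muscle depth.** Depth = 20 mm − ATT; share = (20 − ATT)/20.

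| ATT (mm) | Muscle depth (mm) | Share of path |
|---|---|---|
| 5 | 15 | 75% |
| 10 | 10 | 50% |
| 15 | 5 | 25% |
| 18 | 2 | 10% |
| 20 (eligible) | 0 | 0% |

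**Step 2: a change within a patient.** The documents give no size for ATT change, so 2 mm is an assumption, as is an amplitude proportional to muscle depth.

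- From ATT 5 mm: 13/15 − 1 = −13%
- From ATT 10 mm: 8/10 − 1 = −20%
- From ATT 15 mm: 3/5 − 1 = −40%

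A 2 mm loss gives the mirror image, for example 7/5 − 1 = +40% from 15 mm. The direction of any artefact is therefore as open as the direction of the fat change.

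**Step 3: which outcomes this reaches.** Suppose the signal is multiplied by a constant c.

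- ΔO2Hb and ΔHHb are multiplied by c.
- In equation 1, A and B0 become cA and cB0, and τ is unchanged.
- In TSI = O2Hb/(O2Hb + HHb), c cancels.

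Proportional loss of signal thus reaches only the two amplitude outcomes. An effect on τ or TSI would need fat and muscle signals to be mixed, and the documents do not quantify that.

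**Step 4: which ATT differences matter in which model.** In aim 1 the random intercept absorbs stable differences between patients, so the exposure is within-patient change. The aim 2 ANOVAs have no patient effect. There, differences between patients add noise, and they bias the comparison if ATT differs systematically between regimens.

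**Step 5: illustration for aim 1.** A simulation used 30 patients, 5 visits and no true muscle change. Baseline ATT was uniform on 4 to 14 mm, and each patient's drift varied around the mean with SD 0.3 mm per cycle. Amplitude was 10 × (20 − ATT)/20 with error SD 0.75, and there were 150 runs per setting. The table gives the share of runs rejecting 'no cycle effect' at 0.05.

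| Mean ATT drift (mm per cycle) | Without ATT | With visit-level ATT |
|---|---|---|
| 0 | 6% | 5% |
| 0.25 | 69% | 5% |
| 0.5 | 100% | 5% |
| 1 | 100% | 4% |

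Every setting here is assumed. The adjusted model does well partly because the data were generated with a linear ATT effect. The table shows the mechanism and does not estimate its size in this trial.

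**The case against.** The strongest reply has four parts.

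1. **Scope.** An article condenses the plan, and a SAP may add covariates. This stands to the extent that a missing covariate alone would be a weak point. A SAP cannot, however, supply recordings that the visit procedure prevented, and the match rule is stated in this document.
2. **The match may only check relocation.** The order of photograph, mark, ultrasound and tape fits a check that the same site was found, and no section says a mismatched visit is cancelled. This stands. A reader might infer that visits are being dropped, but the text does not show it. What remains is that the rule does not separate a misplaced probe from a true change in fat.
3. **The main outcome is not reached.** The sample size rests on τ, and Step 3 shows that rescaling leaves τ and TSI alone. This stands. A reader might infer that τ drifts with fat thickness, but nothing in the documents gives such an effect a size.
4. **The numbers are assumed.** No section gives a relation between signal and depth, an ATT distribution or an ATT change. The Introduction names body composition change without site, direction or amount. This stands too, so the percentages and rejection rates are indicative only.

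It is also tempting to say that an eligible patient with 18 mm of fat biases aim 1. By that fact alone she does not, because the random intercept absorbs her stable level. And ATT does have a use beyond matching, as an eligibility criterion at visit 1.

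**Conclusion.** The point holds in limited form. After eligibility, ATT is recorded at every on-off visit, its only stated use is an undefined match to visit 1, and neither stated model contains it. The exposed outcomes are ΔO2Hb and ΔHHb, through within-patient ATT change in aim 1 and also through differences between patients in aim 2.

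The firm size is geometric and comes from the protocol's own depth: 15 mm of sampled muscle at ATT 5 mm, 2 mm at 18 mm and none at the eligible limit. The exclusion limit alone therefore does not keep the concern small. The figures of 13% to 40% for a 2 mm change rest on an assumed change and an assumed proportional signal, and the true relation need not be linear. Bias in τ or TSI, and actual loss of visits, are possible but not shown. This is worth correcting because the remedy uses data the protocol already requires.

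**What to change.** - **Visit procedure.** Keep the ATT comparison as a check on sensor relocation, with a stated tolerance. If the photograph and landmark confirm the site and ATT still differs, record ATT, flag the visit and test.
- **Analysis.** Add visit-level ATT as a covariate: change from the patient's visit 1 value in aim 1, and ATT at that cycle in aim 2. Do this at least as a sensitivity analysis for ΔO2Hb and ΔHHb, and as a check for τ and TSI. Show results with and without ATT, since a linear term only approximates a proportional effect and ATT change may run parallel to cycle number.
- **Reporting.** Give the number of visits lost or flagged for an ATT mismatch, by regimen.
- **Text.** Soften the Discussion's statement that the exclusion limit and placement keep the concern small, and say that sampled muscle falls toward zero near the limit.

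The cost is about one degree of freedom per model, plus some precision where ATT and cycle are correlated. With 26 participants already complete out of a planned 30, the procedural change affects few patients and should be dated, so that visits before and after it can be told apart. The covariate applies to all visits at which ATT was recorded. Dropping the placement check altogether is not needed.

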### Outcome measures

#### Collection of biometrics at each visit.

Study staff will measure O2Hb, HHb, and TSI, via the NIRS PortaMon device during the on-off kinetics protocol. We also will measure ventilatory whole-body components including O_2_ and CO_2_ via the Parvomedics metabolic cart. Participants’ perceived exertion to the exercise will be measured via RPE during every exercise stage.

NIRS data will be collected using Artinis Medical System’s Oxysoft software at a frequency of 10hz. A differential pathlength factor (DPF) value of 4 will be selected, as recommended by Artinis (Einsteinweg, Netherlands). The PortaMon will be placed on the vastus lateralis of participants for a period of at least 10 minutes prior to beginning exercise in accordance with the recommendation of Cortese L, et al. to allow calibration of the PortaMon [53].

Throughout data collection, researchers will closely observe for excess movement from participants that may affect the data collection. These sections will be removed from analysis. After data collection, a moving average with a filter width of 1.5 seconds will be applied to smooth leg movement artifacts that occurred during cycling. Data cleaning and analysis will be conducted using R (R Core Team, 2020] and RStudio (Rstudio Team, 2020].

